#### Study instruments for secondary outcomes

The Inhibitory Control Task will be based on a cue-based ‘Frequent Go/Rare No-Go Paradigms’ [31]. Participants will be directed to respond to pictures contained in circles by ‘pressing the space bar’ and to withdraw responses to pictures contained in squares. The go cue will be presented with 100% consistency with non-aggressive stimuli, and the no-go cue with aggressive stimuli. The task will have 20% no-go cues and 80% go cues, in accordance with the frequent go/rare no-go arrangement, as presented in Table 3. The task will have a single session with five blocks, bringing it up to 250 trials. The task will be administered prior to and following the ICT. The task, prior to and post intervention, will be preceded by 10 trials of practice sessions utilizing non-aggressive stimuli in squares and circles as no-go and go cues, respectively. The participants will be provided feedback on incorrect and correct responses during the practice trials. The practice sessions will not be recorded or scored [18, 20, 32]. Commission and omission errors will be recorded. Based on the results of a research study estimating the reliability of associative Go/No-Go Tasks, our task with 50 trials per block is indicated to have an acceptable reliability between 0.60 and 0.80 [33].

**Table 3 Tab3:** Details of one block of the inhibitory control task

Test	Aggressive Stimuli (AS)		Non-Aggressive Stimuli (NAS)		Duration of Presentation	Total Time
	Proportion	Number [T (/C)]	Proportion	Number [T (/C)]		
Pre-Test	20%	10 (2)	80%	40 (8)	1500 ms	15 Minutes
Post-Test	20%	10 (2)	80%	40 (8)	1500 ms	15 Minutes

*T (/C)* Total Pictures (Pictures Per Category)

The Stimulus Evaluation Task is an explicit, self-paced task which will instruct the participants to evaluate the aggressive pictures on an 11-pointer scale (0 to 10). The selection of pictures utilized during the training sessions and the main task will be determined by the patient’s rating on the Stimulus Evaluation Task. For the ICT, the highest-rated pictures will be used and for the sham training, the lowest-rated pictures will be employed. The 15 pictures not covered during the training will be included in the pre-test and post-test task to investigate the occurrence of generalization, defined as the transfer of inhibitory learning to untrained aggressive stimuli, which may indicate potential generalization of effects beyond the training context to real-world situations [18].

Information will be collected on the type and categories of substances consumed using a semi-structured performa for substance use details. Details regarding the routes of administration will be recorded, along with the age at which substance use began and the total duration of use. Data will be collected on the usual amount consumed per occasion and the typical frequency of use, reported in terms of times per day. The pattern of use will be assessed and characterized based on consistency and compulsivity. Additionally, the individual's involvement with support programs such as Alcoholics Anonymous will be documented, including the duration of participation. The date or time since the most recent substance use will also be noted during the assessment. The proforma was constructed by deriving questions from pre-existing literature focusing on similar areas (see Supplementary File 2).

The type and category of gambling behavior(s), along with the age of onset, duration, frequency, and pattern of engagement, will also be recorded using a semi-structured performa. It will also note the most recent episode of gambling. The financial information including the net amount spent, net losses, and net gains over time, will also be recorded. The proforma was constructed by deriving questions from pre-existing literature focusing on similar areas (see Supplementary File 2).

This South Oaks Gambling Screen (SOGS) [26] will be used to measure the type and the frequency of gambling. It consists of 20 multiple-choice questions that explore several aspects of gambling behavior, including consequences of the activity and its impact on interpersonal relationships and finances. The questionnaire covers a range of gambling activities, including playing cards, dice games, casino gambling, lotteries, bingo, stock market investments, commodities trading, slot machines, poker machines, skill-based games, pull tabs, and wagering on animals or sports events. The results of a validation study provide evidence of construct validity of the English version of the SOGS for screening gambling problems in a multiracial Asian community sample [34]. Even so, to maintain comprehensibility and consistency in questioning, the scale will be translated into Hindi following the World Health Organization (WHO) protocol incorporating the stages of forward translation, expert panel, backward translation, and pre-testing and cognitive interviewing.

The Timeline Followback (TLFB) [35] method is a retrospective assessment tool. It involves asking clients to retrospectively estimate their substance use seven days to two years prior to the interview date. Results showed high test–retest reliability and intraclass correlation coefficients for the scale [36], along with acceptable levels of convergent and discriminant [35].

The Alcohol, Smoking and Substance Involvement Screening Test (ASSIST V3.0) questionnaire has eight questions that rate use of different substances like tobacco, alcohol, cannabis, cocaine, amphetamine-type stimulants, inhalants, sedatives, hallucinogens, opioids, and 'other drugs'. It gives a risk score for each substance of use, ranging from 'low risk', 'moderate risk', to 'high risk' [37]. Studies demonstrate that ASSIST has good to excellent reliability, along with good concurrent, construct, predictive, and discriminant validity [38, 39].

Detailed information on each instrument’s specific measurement variable(s), analysis metric, method of aggregation, and time point for each outcome has been provided in Additional file 2 for primary outcome variables (Table S1) and secondary outcome variables (Table S2).

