### Explanation for the choice of comparator {9b}

ST will be matched with active training in terms of both stimulus exposure and response requirements, but will have the contingency agreement reduced to 50%, thereby preventing the formation of associations between aggressive stimuli and inhibitory responses. Similar studies in the past have used sham training as a comparator where stimuli were presented in a way that prevents any form of association [20, 23, 24]. Some other studies working with a different population have also shown the same [25]. Another reason for the inclusion of sham training in the control group is that while controlling for time and attention, it might provide information into the underlying mechanism of functioning of this intervention—differential effects between the groups, if observed, can be attributed to the formation of implicit inhibitory associations.

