## Intervention and comparator

### Intervention and comparator description {15a}

The training program which will be administered to the experimental group will be an associative Go/No-Go Paradigm with 100% contingency. It is a computerized behavioral intervention that leverages implicit processes to associate no-go responses with aggression-related stimuli, thereby developing habitual links with the goal of reducing aggressive behaviors. The go cues (pictures contained in circles) will be consistently paired with non-aggressive stimuli, and the no-go cues (pictures contained in squares) with aggressive stimuli, maintaining 100% contingency. Participants will be instructed to respond to stimuli in accordance with the format of the pictures. They will be directed to respond to pictures contained in circles by ‘pressing the space bar’ and to withdraw from responding to pictures contained in squares. The presentation of stimuli will be interspersed with brief intervals of 1000 ms (ms) featuring cross slides, termed ‘inter-trial’ periods. The intervention will be presented on Microsoft® PowerPoint for Mac (Version 16.78.3) software. The training program will be structured into six sessions, spanning three consecutive days, with two sessions delivered on each day. These sessions will progressively increase in complexity [28], in terms of reducing the probability of ‘No-Go’ stimuli and decreasing stimulus response duration (see Table 1).

**Table 1 Tab1:** Session-by-session plan for inhibitory control training

Training Session	Aggressive Stimuli (AS)		Non-Aggressive Stimuli (NAS)		Duration of Presentation (ms)	Total Time (Minutes)
	Proportion	Number [T (/C)]	Proportion	Number [T (/C)]		
Training Session—1	70%	35 (7)	30%	15 (3)	3000	15
Training Session—2	70%	35 (7)	30%	15 (3)	2500	15
Training Session—3	50%	25 (5)	50%	25 (5)	2500	15
Training Session—4	50%	25 (5)	50%	25 (5)	2250	15
Training Session—5	30%	15 (3)	70%	35 (7)	2250	15
Training Session—6	30%	15 (3)	70%	35 (7)	2000	15

*T (/C)* Total Pictures (Pictures Per Category), *ms* Milliseconds

Each session will consist of five blocks, and each block will comprise 50 trials. This structure will result in a total of 1500 trials throughout the training program. The choice of aggressive (no-go) and non-aggressive (go) stimuli employed in each training session will be determined by a Stimulus Evaluation Task, individualized to each participant [18].

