The sham training administered to the control group will employ an associative Go/No-Go Paradigm with 50% contingency instead of 100% (see Fig. 2). Go and no-go cues will be split equally between aggressive and non-aggressive stimuli. Participants will receive the same instructions and the same method of presentation of the intervention. During the practice sessions, participants will not receive feedback on correct and incorrect responses. These sessions will not progressively increase in complexity, as shown in Table 2. The training will also be organized into six sessions, spread out over three consecutive days, with two sessions per day. Each session will consist of five blocks, and each block will comprise 50 trials. This structure will result in a total of 1500 trials throughout the training program. The choice of aggressive (no-go) and non-aggressive (go) stimuli employed in each training session will be determined by a Stimulus Evaluation Task [18].

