### How will be blinding be achieved {24b}

Participant blinding will be achieved by ensuring that the experimental and sham training procedures are the same in appearance, duration, session structure, instructions, and mode of delivery. Both conditions will have identical computerized Go/No-Go tasks administered over six sessions across three consecutive days, using similar stimuli and response requirements, but different association contingencies. Participants will be informed that they will receive either an active or a sham version of the training, without disclosure of the specific feature of contingency distinguishing the two conditions.

Given that the intervention is designed to operate through implicit learning mechanisms by unconsciously forming associations between aggressive stimuli and inhibitory responses, it would not be appropriate to explicitly inform participants that the intervention targets aggression. Hence, the participant information sheet has described the study as follows: *“You are invited to participate voluntarily in a research study focused on providing a psychological intervention aimed at alleviating symptoms associated with substance use through the use of visual stimuli.” This will be cleared out at the end of the study when the participants will be informed regarding the true nature of the study and why it was required by the investigators to avoid disclosure of the same, at the beginning.* Prior to this and following the final follow-up, participants will be asked to guess their allocation group, either control or experimental, which will aid in assessing the effectiveness of the trial's blinding. They will also be asked about their perception of whether the intervention they received influenced their levels of aggression.

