### Methods for additional analyses (e.g. subgroup analyses) {27d}

After the completion of data collection, the data will be reviewed for suitability of the following analyses: Post hoc comparisons may be conducted for detailed analysis through between group and within group measures in case prior statistical analysis indicates significant differences. The moderating effect of changes in inhibitory control and stimulus devaluation immediately post intervention on changes in overt aggression behaviours at 1-month and 3-months post-intervention may be analysed.

The moderating effect of changes in inhibitory control and aggressive behaviour immediately following the intervention and at 1-month post-intervention on changes in substance use frequency and gambling behaviour at 1-month and 3-months post-intervention may be analysed.

If a significant dropout rate occurs during the study, an analysis can be conducted to identify any patterns or trends in the characteristics of participants who dropped out. This analysis can help understand potential reasons for dropout in terms of demographic, clinical, or other factors associated with higher dropout rates.

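### ICT and sham differ in picture intensity, timing and progression as well as contingency, so a group difference cannot be credited to contingency alone, and ratings of picture subsets regress in opposite directions by arm

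*Protocol article*

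**What the plan says.** All references are to the protocol article.

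**Claims of sameness.** Explanation for the choice of comparator {9b} states that "ST will be matched with active training in terms of both stimulus exposure and response requirements", with the contingency reduced to 50%, and concludes that "differential effects between the groups, if observed, can be attributed to the formation of implicit inhibitory associations". How will be blinding be achieved {24b} adds that "the experimental and sham training procedures are the same in appearance, duration, session structure, instructions, and mode of delivery".

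**Stated differences.**
- Study instruments for secondary outcomes, on picture choice: "For the ICT, the highest-rated pictures will be used and for the sham training, the lowest-rated pictures will be employed".
- Intervention and comparator description {15a}, on ICT: "These sessions will progressively increase in complexity". On sham: "These sessions will not progressively increase in complexity, as shown in Table 2".
- Table 1 (ICT) lowers the aggressive, and therefore no-go, share from 70% to 30% and the presentation time from 3000 to 2000 ms. Table 2 (sham) holds 50% and 3000 ms in all six sessions.

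**Picture-based outcomes.** On untrained pictures: "The 15 pictures not covered during the training will be included in the pre-test and post-test task to investigate the occurrence of generalization". Expected outcomes plans to test generalisation with ratings of stimuli left out of the intervention. Methods for additional analyses {27d} names "changes in inhibitory control and stimulus devaluation immediately post intervention" as possible moderators of later change in aggression.

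**The concern.** A sham arm isolates one ingredient only if the other ingredients are shared. Here the two arms also differ in how strongly the pictures were rated, how long they are shown and whether the task becomes harder. If ICT does better, any of these could be the reason. This matters because Sample size {19} describes the control group mainly as a means of studying how ICT works, and Trial design {12} names how it works as an interest of the trial.

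The picture rule also reaches the picture-based measures. Training pictures are selected on the baseline rating, the same quantity whose change is to be measured, and from opposite ends of the scale in the two arms. Extreme ratings drift back towards the mean on retest, so the arms drift in opposite directions even if training does nothing. The untrained pictures used to test generalisation are likewise drawn from opposite ends.

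**Working it through.** **1. Session time.** Inputs: Tables 1 and 2; five blocks of 50 trials, so 250 trials per session; a 1000 ms interval between trials ({15a}, taken to apply to both arms because sham uses the same method of presentation). Assumption: each picture stays on screen for its tabled duration. Session time = 250 × (presentation + 1 s).

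| Session | ICT (ms) | ICT (min) | Sham (ms) | Sham (min) | Table label (min) |
|---|---|---|---|---|---|
| 1 | 3000 | 16.7 | 3000 | 16.7 | 15 |
| 2 | 2500 | 14.6 | 3000 | 16.7 | 15 |
| 3 | 2500 | 14.6 | 3000 | 16.7 | 15 |
| 4 | 2250 | 13.5 | 3000 | 16.7 | 15 |
| 5 | 2250 | 13.5 | 3000 | 16.7 | 15 |
| 6 | 2000 | 12.5 | 3000 | 16.7 | 15 |
| Total | | 85.4 | | 100.0 | 90 |

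The plan's own figure of 15 minutes is not reproduced for any session, and the two arms do not have the same duration.

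**2. Aggressive-picture screen time.** Five blocks × sum of (number × seconds):
- ICT: 5 × (35×3 + 35×2.5 + 25×2.5 + 25×2.25 + 15×2.25 + 15×2) = 5 × 375 = 1875 s.
- Sham: 5 × 6 × 25 × 3 = 2250 s, which is 20% more.

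**3. What does match.** Total trials: 6 × 250 = 1500 in each arm. Aggressive presentations: ICT 175+175+125+125+75+75 = 750; sham 6 × 125 = 750. No-go trials: 750 in each arm, reading the sham's equal split as half of each picture type. The pattern over sessions differs (ICT 175 falling to 75, sham 125 throughout). Aggressive/no-go pairings are 750 against 375, which is the intended contrast.

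**4. Regression to the mean in ratings.** The pool size is not stated. A pool of 50 is assumed (35 trained in ICT sessions 1 and 2, plus 15 untrained). Ratings are assumed normal with retest reliability *r*, and there is no treatment effect. ICT trains on the top 35 and sham on the bottom 25. In simulation the baseline ratings of trained pictures then differ by about 1.27 picture-level SD between arms. The expected spurious difference in change is (1 − *r*) × 1.27 SD; at *r* = 0.8 this is 0.2 × 1.27 ≈ 0.25, against 0.26 simulated.

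| Reliability (assumed) | Trained pictures, favouring ICT (SD) | Untrained pictures, against ICT (SD) |
|---|---|---|
| 0.95 | 0.06 | 0.11 |
| 0.8 | 0.26 | 0.46 |
| 0.6 | 0.51 | 0.91 |

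The untrained column takes the 15 lowest-rated pictures in ICT and the 15 highest-rated in sham. At reliability 0.8, pools of 40 to 100 give 0.16 to 0.46 SD on trained pictures. For the mean over the whole picture set, the simulated false-positive rate was about 4 to 6% at a nominal 5%, so the artefact is absent there.

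**5. The count of untrained pictures.** If one pool of 50 serves both arms and sessions reuse the same ranked set, ICT leaves 50 − 35 = 15, but sham leaves 50 − 25 = 25. The stated 15 then fits ICT only.

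**The case against.** The matching claim is partly true: trial, aggressive-picture and no-go totals agree, and the article says openly that sham does not progress. The mechanism claim is hedged in several places. The comparator and strengths sections say only that sham might inform on mechanism, Trial design {12} calls some aspects exploratory, Sample size {19} reports uncertainty about specificity, and the {27d} analyses are optional. All of this stands. It softens the problem, but it does not reconcile Tables 1 and 2 and the picture rule with the statements on attribution and on identical duration and session structure.

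Some stronger readings are tempting but unsupported:
- **That the arms differ in feedback.** Sham practice is said to have none, but nothing says ICT training gives it. The feedback described elsewhere belongs to the assessment task, without distinction by arm. This is an ambiguity, not a shown difference.
- **That devaluation is bound to favour ICT.** This depends on which pictures are scored. The artefact reverses on untrained pictures, the subset Expected outcomes describes for generalisation, and vanishes for a whole-set mean. The exact metrics are in Additional file 2, which is not at hand.
- **That commission errors carry a bias of known size.** The untrained pictures are said to be included in the test, not to make up all of it, and comparing pre-test with post-test on the same pictures removes any constant intensity effect. What can be shown is that the stimuli are not comparable between arms.

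**Conclusion.** The contradiction is in the document itself and needs no assumption about the pool. The arms differ in picture intensity, presentation time and progression as well as contingency. Task time is 85.4 against 100.0 min, and aggressive-picture time 1875 against 2250 s. A group difference therefore reflects the whole ICT package and cannot be credited to contingency alone.

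A reader might infer that the primary result is compromised. It is not on this point: the OAS-M is not picture-based, and the comparison of the two packages on it stands.

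For ratings, opposite regression to the mean follows from the selection rule whenever a trained or untrained subset is scored and reliability is below 1. Its direction is firm; its size rests on the assumed reliability, normality and pool of 50. The untrained pictures are lower-rated in ICT and higher-rated in sham, so the generalisation comparison is not like with like. The mismatch in the count of 15 also depends on the assumed pool and on reuse of one ranked set.

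**What to change.** 1. In {9b}, {24b} and Expected limitations and strengths, state that a group difference reflects the ICT package as a whole. If the contingency claim is to stay, reconcile {9b}, {15a} with Tables 1 and 2, the picture rule under secondary outcomes, and {24b}, so that both arms share one picture-selection rule and one session structure.
2. Score stimulus devaluation as the mean rating over the full rated picture set, by the same rule in both arms and adjusted for baseline. Do not score it on subsets selected by baseline rating.
3. Report the between-arm comparison on untrained pictures as confounded with picture intensity.

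The cost is a weaker mechanism claim and a full-set score that dilutes any effect specific to trained pictures. Apart from the alternative in step 1, training is left as it is.

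Holding out 15 pictures at random within rating strata may look like a simple alternative, but it would change training. With a pool of 50, only 35 would remain and ICT sessions 1 and 2 need all of them, so ICT would no longer train on the highest-rated pictures. If done before allocation, it would also move the rating task ahead of randomisation, contrary to Participant timeline {18}, with enrolment open since January 2025.

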#### Participant timeline {18}

Patients admitted to the National Drug Dependence Treatment Centre (NDDTC) will be administered upon a brief screening process. The screening will initiate only when the participant is able to actively engage in the study, ensuring they are not intoxicated or in a state of withdrawal. Withdrawal charting will be done using the Clinical Institute Withdrawal Assessment of Alcohol Scale, Revised (CIWA – Ar) [40] for alcohol, Clinical Opiate Withdrawal Scale (COWS) [41] for opioids, Minnesota Nicotine Withdrawal Scale (MNWS) [42], the Cannabis Withdrawal Scale (CWS) [43] for cannabis, and the Clinical Institute Withdrawal Assessment Benzodiazepines (CIWA—B) [44] scale for Benzodiazepines. If the participant is found intoxicated or experiencing withdrawal, the screening process will be paused. It will be resumed only after a reassessment of withdrawal symptoms has been conducted within the next 24–48 h.

Patients diagnosed with substance use disorder by a psychiatrist will then undergo the South Oaks Gambling Screen (SOGS) for the identification of problem or pathological gambling in the patients. Once it is ascertained that the participant fulfills the inclusion/exclusion criteria, written consent will be taken by the primary investigator, and patients will be randomized to either the experimental or control group. The Alcohol, Smoking, and Substance Involvement Screening Test (WHO-ASSIST Version 3.0) and the Overt Aggression Scale – Modified (OAS – M) will be administered along with the sociodemographic and clinical proformas. Other baseline assessments, including the Stimulus Evaluation Task, Inhibitory Control Task, and the Timeline Follow-Back Scale (TLFB) will also be performed post randomization. All questionnaires and assessments will be administered by verbally posing the questions (and options) to the patients. The demographic details, medical/psychiatric history of the participant, their family history, and treatment record will also be recorded (see Supplementary File 2).

Subsequently, the experimental and control group participants will undergo the inhibitory control training or sham training for 3 consecutive days, respectively, administered by the primary investigator (psychologist) for all patients. Throughout this period, the study participants will continue to receive concurrent treatment as usual as per the advice of the clinical treating team. Any changes in the medication that occur during the study period will be recorded.

One day after the intervention, participants will be assessed using the outcome measure administered during the baseline assessment. The first follow-up will be held at 1 month post-intervention (± 4 Days), and the second follow-up will be held at 3 months post-intervention (± 7). A comprehensive record of treatment prescribed to the participants will be maintained throughout the study period. After the final follow-up, participants will be prompted to guess their allocation group, either control or experimental, which will aid in assessing the effectiveness of the trial's blinding. They will also be asked about their perception of whether the intervention they received influenced their levels of aggression. The instrument administration and study timeline has been summarized in Fig. 3.

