### Outcomes {16}

#### Study instruments for primary outcomes

The Overt Aggression Scale‐Modified [29, 30] is a semi-structured interview designed to evaluate various categories of aggressive behaviors. Four sub-components make up the overall aggression (AGG) score: Verbal Aggression, Aggression Against Object, Aggression Against Others, and Aggression Against Self. Subcomponent scores are determined by multiplying the number and severity level of aggressive behaviors of each type during the prior week. Additional scores include a Global Anger and Aggression (GAA) score composed of two item ratings: Subjective experience of anger and overt expression of anger. The OAS‐M has been shown to be reliable and valid, with good psychometric properties in terms of internal consistency, inter-rater reliability, test–retest reliability, face validity, convergent validity, divergent validity, and discriminant validity [30]. The primary outcome of the study will be the change in overall aggression score from baseline to the 1-Month post-intervention follow-up, as measured using the Overt Aggression Scale–Modified (OAS-M), and will be summarized using mean values and standard deviations.

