### Allocation concealment mechanism {22}

Allocation concealment will be ensured using the Sequentially Numbered, Opaque, Sealed Envelopes (SNOSE) [52] method. The random allocation sequence will be placed into sealed envelopes by a researcher not involved in participant enrolment or intervention delivery. Envelopes will be opened sequentially only after a participant has provided written informed consent.

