## Assignment of interventions: blinding

### Who will be blinded {24a}

Only trial participants will remain blinded to allocation throughout the study period, making it a single-blind study. Investigator blinding was not feasible, as all aspects of participant enrolment, intervention delivery, outcome assessment, and analysis are conducted by a single investigator.

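### The baseline OAS-M is taken after the envelope is opened, by the investigator who then knows the arm, so the starting point of the primary outcome is exposed to an avoidable risk of rater bias

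*Protocol article*

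**What the plan says.** Participant timeline {18} describes the order of events. Once eligibility is settled, "written consent will be taken by the primary investigator, and patients will be randomized to either the experimental or control group". The next sentence says that the ASSIST and the OAS-M "will be administered along with the sociodemographic and clinical proformas". The sentence after that reads: "Other baseline assessments, including the Stimulus Evaluation Task, Inhibitory Control Task, and the Timeline Follow-Back Scale (TLFB) will also be performed post randomization".

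Allocation concealment mechanism {22} makes consent the only condition for opening an envelope: "Envelopes will be opened sequentially only after a participant has provided written informed consent". Implementation {23} states that opening it is the moment when the primary investigator learns the group. Plans for assessment and collection of outcomes {25a} has the primary investigator administer all assessments, baseline included. Who will be blinded {24a} explains that only participants are blinded because "all aspects of participant enrolment, intervention delivery, outcome assessment, and analysis are conducted by a single investigator".

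On the endpoint, the Outcomes section says: "The primary outcome of the study will be the change in overall aggression score from baseline to the 1-Month post-intervention follow-up". The OAS-M "is a semi-structured interview designed to evaluate various categories of aggressive behaviors", and its scoring is described thus: "Subcomponent scores are determined by multiplying the number and severity level of aggressive behaviors of each type during the prior week".

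**The concern.** The OAS-M depends on how the interviewer probes, what is counted as an aggressive act and what severity it is given. An interviewer who knows the arm, in a trial whose Expected outcomes section anticipates less aggression after active training, may probe or score differently by arm without meaning to. At follow-up the protocol accepts this exposure because one person does everything. At baseline that reason does not apply: until the envelope is opened, the same person does not know the arm. The stated order gives up the one OAS-M rating that a single-investigator trial can keep blind.

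Two consequences follow.

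- A rating difference at baseline becomes part of the change from baseline. The planned baseline comparison, with possible adjustment for initial differences (Statistical methods {27a}), would treat it as chance imbalance.
- The primary analysis includes everyone randomised {27b}. A patient who leaves between envelope and baseline is therefore in the analysis set without a starting value.

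**Working it through.** **Order of events.** The plan states no figure for this point, so the main check is to set the sections side by side.

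1. {18}: consent, then randomisation, then OAS-M and ASSIST.
2. {18}, next sentence: the remaining baseline measures come after randomisation as well. Its opening word, and the word for as well, carry the same timing to the OAS-M and ASSIST just listed.
3. {22}: the envelope waits for consent and for nothing else.
4. {23}: opening it shows the arm to the primary investigator.
5. {25a} and {24a}: that investigator, unblinded, makes all assessments.
6. Trial design {12} and {25a} call the baseline pre-intervention. That means before training, not before allocation.

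No section places the baseline OAS-M before the envelope or gives it to a blinded rater.

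**Illustration of size.** The documents give no size for a rating shift, so the shift b (the arm difference in baseline scoring, in OAS-M points) is an assumption, shown over a range. Other inputs come from Sample size {19}: SD 3.89 before and 1.92 after in the cited study, assumed correlation 0.5, and 26 completers or 65 randomised per arm.

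- SD of change = √(3.89² + 1.92² − 2 × 0.5 × 3.89 × 1.92) = √11.35 = 3.37. As a check, (3.44 − 1.07)/3.37 = 2.37/3.37 = 0.70, which reproduces the plan's effect size.
- Unadjusted change-score contrast: bias = b.
- Baseline-adjusted contrast (ANCOVA): bias = slope × b, with slope = 0.5 × 1.92/3.89 = 0.247. Residual SD = 1.92 × √(1 − 0.5²) = 1.66.
- Two-sided 5% false-positive rate with no true effect, normal approximation: 1 − Φ(1.96 − z) + Φ(−1.96 − z), where z = bias/(SD × √(2/n)).

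Example: for b = 1 and n = 26, unadjusted, z = 1/(3.37 × √(2/26)) = 1/0.934 = 1.07, and the rate is 18.8%.

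| Assumed b (points) | Unadjusted bias (points; share of change SD) | Adjusted bias (points) | False positives, unadjusted, 26 / 65 per arm | False positives, adjusted, 26 / 65 per arm |
|---|---|---|---|---|
| 0.25 | 0.25; 0.07 | 0.06 | 5.8% / 7.1% | 5.2% / 5.5% |
| 0.5 | 0.5; 0.15 | 0.12 | 8.3% / 13.5% | 5.8% / 7.1% |
| 1.0 | 1.0; 0.30 | 0.25 | 18.8% / 39.5% | 8.3% / 13.5% |
| 1.5 | 1.5; 0.45 | 0.37 | 36.2% / 71.8% | 12.6% / 24.5% |

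The table treats follow-up scoring as unbiased, so it isolates what a baseline shift alone would do.

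**The case against.** Several points can fairly be made for the plan.

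- **The timing is partly inferred.** The sentence that says post randomisation outright names the Stimulus Evaluation Task, Inhibitory Control Task and TLFB, not the OAS-M. The schedule figure and the additional file with outcome time points are not available here, and {22} sets an earliest moment for opening the envelope, not an exact one. This stands as a caution. The sentence order in {18} is still clear, and nothing shown contradicts it.
- **Adjustment shrinks the bias.** A reader might infer that any baseline shift passes in full into the treatment effect. That holds only without baseline adjustment. On the {19} inputs, ANCOVA leaves about a quarter of it. But {27a} only says that adjustment will be considered, and it would not remove the bias.
- **The baseline is still before training, and participants are blinded.** Correct, so only the rater's expectations can act. The Inhibitory Control Task, scored by commission and omission errors, leaves little room for them.
- **Loss between envelope and baseline may be rare.** Patients are in hospital and no interval is stated. This stands: it is a possibility of unknown frequency. The plan does, however, foresee patients leaving against medical advice {15b}.
- **The larger exposure is elsewhere.** The 1-month OAS-M is rated, and the data analysed, by the same unblinded person, as {24a} discloses. Reordering does not touch that. It limits the gain but is no reason to leave the baseline exposed as well.

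**Conclusion.** The point holds as an avoidable risk to the primary endpoint. As written, the baseline OAS-M, ASSIST and TLFB are taken after allocation by someone who knows the arm, and the expected limitations do not mention it.

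A reader might go further and infer that the primary result will be biased, or biased in favour of active training. The documents do not support that: they give neither size nor direction for any rating shift. The 0.5- and 1-point figures are assumptions; only the SDs and the correlation come from the plan. Nor should the shifts be read as shares of an expected difference between arms, because the 2.37 points in {19} is a within-group change in a cited study.

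Under those assumptions, the bias would be 0.5 or 1 point without baseline adjustment (0.15 or 0.30 of the change SD) and about 0.12 or 0.25 points with it.

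**What to change.** Amend {18} and {22} so that the next envelope is opened only after written consent and after the OAS-M, ASSIST, TLFB and Stimulus Evaluation Task have been completed and recorded. Note the date and time of both the baseline and the envelope opening. The SOGS needs no change, because it is part of screening and already precedes randomisation. The Stimulus Evaluation Task can move because the ratings themselves do not need the arm; only the later choice of training pictures does.

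The baseline Inhibitory Control Task is different. It includes pictures left out of training, and training uses the highest-rated pictures in one arm and the lowest-rated in the other, so the left-out set may depend on arm. Move this task before the envelope only if its pictures are chosen by a rule that does not depend on arm.

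In the report, give the number of participants enrolled under each order with an exploratory comparison, which will have little power given the planned 60% attrition. State that follow-up ratings remained unblinded.

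The cost is no added staff or procedure, but an amendment during enrolment (begun January 2025, expected to end December 2026). It needs ethics committee approval and the consent of all seven Doctoral Committee members. Participants already enrolled under the present order cannot be repaired.
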